### Observer blinding

All measurements (baseline, post intervention and 1 year review) will be made by an independent assessor (CB) blind to the treatment allocation.

### Intervention

The cardiac rehabilitation group will participate in a 10 week programme including 8 weeks physiotherapy led (OL), individually tailored aerobic exercise for one hour twice weekly at up to 60% of their maximal heart rate. They will receive a two hour didactic lecture addressing modifiable risk factors for stroke and stress management (OL and AC). In addition individual brief smoking cessation counselling, exercise and dietary advice (OL) including information leaflets in accordance with the WHO guidelines for secondary prevention in low and medium resource settings [44] will be provided to those failing to meet the recommended guidelines.

To minimise the Hawthorne effect, the control group will attend the two hour risk reduction lecture as outlined above.

### Participant Recruitment

Subjects with ischaemic stroke will be recruited from the outpatient Stroke Rehabilitation Unit, Baggot Street Community Hospital, from the 4 community based stroke support groups. TIA subjects will be recruited from a TIA clinic in a tertiary hospital in the greater Dublin. Information leaflets will be distributed to potential subjects fulfilling the inclusion criteria in the Stroke Rehabilitation Unit database, Baggot Street Community Hospital and TIA clinic in AMNCH Hospital, with the consent of the Consultant Neurologist in this centre. Interested subjects will then contact the principle researcher (OL) should they wish to participate. Talks will be given at each support group branch meeting and information leaflets distributed. Participants will then be screened by phone to ensure they fulfil the inclusion criteria and that none of the exclusion criteria apply. The American College of Sports Medicine PARQ [22] questionnaire will be incorporated in the screening process to exclude subjects unsuitable for exercise testing. The General Practitioners of those attending the support groups will be contacted to give permission for patients to attend the programme and to consent to access medical records where necessary. A one week period between the information dissemination and consent will be given to allow due time for participants to consider the study.

### Inclusion Criteria

Medically stable post ichaemic stroke or (> 3 months) post TIA, referred from specialist tertiary centres. > 1 year post ischaemic stroke with G.P. consent from community services. Over 18 years of age of either sex.

### Exclusion Criteria

O2 dependence, angina, unstable cardiac conditions, unstable diabetes, major medical conditions, claudication, febrile illness, pregnancy or cognitive impairment.

**Sample size calculations **based on the ability to detect significant differences in the key outcome variables with 80% power and p < 0.05 are indicated in table 1. Cardiac risk data was taken from the pilot study and adherence to European guidelines for lifestyle participation in a high risk CVD group was taken from baseline data of the first 50 subjects recruited to the CRAFTS trial. The formulae for detecting change in % was n > = K [P_1_(1 - P_1_) + P_2 _(1-P_2_)]/Δ^2^. The formula for detecting a change in means was n >= 2Kσ^2^/Δ^2^K = 7.8. Our pilot study [27] resulted in a withdrawal rate of 5% overall. Based on primary outcome measures of adherence to all three European lifestyle guidelines and cardiac risk score reduction with an anticipated drop-out rate of 10%, 144 participants will be recruited. 72 randomised to the intervention group and 72 to the control group.

**Table 1 T1:** Sample size calculations

	**% adherence to European Guidelines on CVD prevention in high risk group(CRAFTS baseline data)**		**Target change to detect %**	**Sample size per group**
Moderate or vigorous exercise for 20 mins 3 or more times/week	17		Increase by 20%	73
Dietary intake of 3 vegetables portions & 2 fruit portions or more/day	21		Increase by 20%	80
No smoking % in stroke and TIA patient population	85		Increase by 15%	61
% subjects fulfilling all 3 criterion	9		Increase by 20%	56
	**Mean (sd) of baseline measures from pilot study in stroke patients**	**Mean change in intervention group – pilot study**	**Target change to detect**	
Cardiac Risk Score	9.4 (6.80)	1.52	4.0	72
VO2 exercise test	10.87 (1.71)	1.48	1.0	46
HAD – Anxiety subscale	6.13 (3.71)	0.86	1.5	54

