**Methods:**

A single blind randomised controlled trial is proposed to examine a primary care cardiac rehabilitation programme for adults post transient ischemic attack (TIA) and stroke in effecting a positive change in the primary outcome measures of cardiac risk scores derived from Blood Pressure, lipid profile, smoking and diabetic status and lifestyle factors of habitual smoking, exercise and healthy eating participation. Secondary outcomes of interest include health related quality of life as measured by the Hospital Anxiety and Depression Scale, the Stroke Specific Quality of Life scale and WONCA COOP Functional Health Status charts and cardiovascular fitness as measured by a sub-maximal fitness test.

A total of 144 patients, over 18 years of age with confirmed diagnosis of ischaemic stroke or TIA, will be recruited from Dublin community stroke services and two tertiary T.I.A clinics. Exclusion criteria will include oxygen dependence, unstable cardiac conditions, uncontrolled diabetes, major medical conditions, claudication, febrile illness, pregnancy or cognitive impairment. Participants will be block-statified, randomly allocated to one of two groups using a pre-prepared computer generated randomisation schedule. Both groups will receive a two hour education class on risk reduction post stroke. The intervention group will receive a 10 week programme of supervised aerobic exercises (twice weekly) and individually tailored brief intervention lifestyle counselling. Both groups will be tested on week one and week ten of the programme. Follow-up at 1 year will assess longer term benefits. Analysis will test for significant changes in the key variables indicated.

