### Data Collection and Statistical Analysis

Data collected will be recorded on a pro-forma collection sheet and will be entered onto Microsoft Excel and the Statistical Package for the Social Sciences (SPSS v12.0). Analysis will be conducted on an intention to treat basis and withdrawals from the programme will be followed up to ensure complete data. A last measurement carried forward method will be used to predict outcome where drop-outs occur [46]. Baseline data will be reported using descriptive and frequency statistics.

Change scores occurring over the 10 week trial period and between baseline and 1 year will be compared between intervention and control groups using:

▪ Independent t tests and one-way ANOVA where data are interval or ratio level and conform to the assumptions of normality i.e. Cardiac Risk Score, VO2, Maximal work output (Watts), Peak Pressure Rate Product, Lipid profile (Total Cholesterol, HDL, LDL, Triglyceride).

▪ Non-parametric tests (Mann Whitney and Kruskall Wallis tests) will be used for ordinal level data (Hospital Anxiety and Depression Scale, Stroke Specific QoL) or where a normal data distribution is not found.

▪ Categorical variables will be analysed using Chi square tests (% smoking, % taking moderate and vigorous exercise 3 times per week, % meeting 2 fruit/3 veg daily guidelines).

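### Adherence to all three lifestyle guidelines is named as a primary basis for the sample size but is missing from the listed outcomes and tests, and two of the three components listed instead need more than the 72 per group

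*Protocol article*

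**What the plan says.** The sample size paragraph of the protocol article (printed under Exclusion Criteria) rests the total on two outcomes: "Based on primary outcome measures of adherence to all three European lifestyle guidelines" and, in the same sentence, a reduction in the cardiac risk score. It continues "with an anticipated drop-out rate of 10%, 144 participants will be recruited", with 72 per group. Table 1 has a row for the share of subjects meeting all three criteria: 9% at baseline, an increase of 20 points, 56 per group. It also has a row for each guideline: exercise 73 per group, diet 80, non-smoking 61.

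The other places that list lifestyle outcomes do not name the composite:

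- The abstract's Methods gives the primary lifestyle outcomes as "lifestyle factors of habitual smoking, exercise and healthy eating participation".
- Aim (ii) speaks of adherence to the European guidelines and then gives smoking, diet and exercise one by one, as examples.
- Table 2 lists the three behaviours in separate entries.
- The analysis section states "Categorical variables will be analysed using Chi square tests (% smoking, % taking moderate and vigorous exercise 3 times per week" and ends that list with the fruit and vegetable guideline.

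The exercise criterion also varies. Table 1 uses "Moderate or vigorous exercise for 20 mins 3 or more times/week". Aim (ii) joins the two intensities with and/or. Table 2 and the analysis section join them with a plain and, without the 20-minute threshold.

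**The concern.** One document describes the lifestyle primary outcome in two ways: a single composite where the trial is sized, and three separate variables where outcomes and tests are listed. The choice decides whether there are two primary comparisons (composite and cardiac risk score) or four (three components and cardiac risk score). If it stays open until the data are in, a composite result and three component results will all be available, and the protocol will not say which one carries the conclusion. If the components are primary, as the abstract has it, two of them are tested with fewer patients than Table 1 requires.

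**Working it through.** **Inputs.** All come from the sample size paragraph and Table 1: 80% power, p < 0.05, K = 7.8, 10% drop-out, 72 per group. The increases are read as absolute percentage points, because only that reading reproduces the table.

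**Reproducing the rows.** Formula: n ≥ K[P1(1−P1) + P2(1−P2)]/Δ².

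- Exercise, 17% to 37%: 7.8 × (0.1411 + 0.2331)/0.04 = 72.97, so 73. Printed 73.
- Diet, 21% to 41%: 7.8 × (0.1659 + 0.2419)/0.04 = 79.5, so 80. Printed 80.
- All three, 9% to 29%: 7.8 × (0.0819 + 0.2059)/0.04 = 56.1. Printed 56.
- Non-smoking, 85% to 100%: 7.8 × (0.1275 + 0)/0.0225 = 44.2, so 45. Printed 61; not reproduced.
- Cardiac risk score, n ≥ 2Kσ²/Δ²: 2 × 7.8 × 6.80²/4.0² = 45.1, so 46. Printed 72; not reproduced.

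The last two mismatches are a separate matter. They do not affect the exercise, diet and composite rows, which reproduce.

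**Power at the planned size.** With all 72 analysed n = 72; after 10% drop-out 72 × 0.9 = 64.8, taken as 65. Power = Φ(Δ/√{[P1(1−P1) + P2(1−P2)]/n} − 1.96). For diet at 72: √(0.4078/72) = 0.0753; 0.20/0.0753 − 1.96 = 0.70; Φ(0.70) = 0.76.

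| Outcome | n = 72 | n = 65 |
|---|---|---|
| Exercise | 79% | 75% |
| Diet | 76% | 71% |
| Non-smoking | 95% | 92% |
| All three | 89% | 85% |
| Cardiac risk score (SD 6.80, change 4.0) | 94% | 92% |

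Using the pooled variance lowers the proportions slightly: exercise 78% and 73%, diet 74% and 70%, all three 87% and 84%. A continuity-corrected chi-square, by exact enumeration, gives exercise 72% and 67%, diet 69% and 63%, all three 83% and 79%.

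**Size needed for 80% power after 10% drop-out.** Diet 80/0.9 = 88.9, so 89 per group (178 in total). Exercise 73/0.9 = 81.1, so 82 per group (164). All three 57/0.9 = 63.3, so 64 per group, which the planned 72 covers.

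**The other reading of the phrase.** If adherence to all three guidelines means each guideline on its own, the largest row governs. That is diet, at 80 per group before drop-out, and 72 is too few. If it means the composite, 72 is enough but the composite is not among the listed tests. The sample size paragraph and the outcome and analysis sections disagree on either reading.

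**The case against.** - **What sets the 72.** A reader might infer that the composite alone sets the sample size, so that the trial never tests what it was sized on. The text does not support this. The composite is named together with the cardiac risk score and gives only about 63 or 64 per group with drop-out. The 72 equals the printed cardiac risk row, and that outcome has a planned t test.
- **Reach of the power problem.** A reader might also infer that 80% power fails for the planned tests in general. It does not: non-smoking and the cardiac risk score exceed 80% on their stated inputs. Nor does the paragraph claim that 144 gives 80% power for exercise or diet; it prints 73 and 80 openly. The difficulty comes from the abstract making those components primary.
- **Number analysed.** The plan is intention to treat, with follow-up of withdrawals and last measurement carried forward, so 72 per group is the number analysed. On that basis exercise is one patient per group short, which is negligible, and diet is about 4 points short of 80%. The 65-per-group figures are the less favourable case.
- **Whether the composite is truly absent.** Aim (ii) gives the components as examples, Table 2 need not list a derived variable, and the general chi-square rule could cover a yes/no composite. That is fair, so it cannot be said for certain that the composite would go untested. But no place outside the sample size paragraph and Table 1 names it, and a primary outcome should not have to be inferred.
- **The composite's target.** Table 1 implies that 9/17 = 53% of those meeting the exercise guideline meet all three. If exercise reached 37% and that share stayed at 53% (an assumption), the composite would reach about 19.6%, with power of about 45% at 72 and 42% at 65 per group. The 85% to 89% depends on the stated target.
- **Exercise wording.** Aim (ii) already says and/or, so the plain and elsewhere may be loose drafting. It still needs aligning.

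**Conclusion.** The point holds in a limited form. The lifestyle primary outcome named in the sample size paragraph does not appear in the abstract's primary outcomes, aim (ii), Table 2 or the listed tests. Of the three components that appear there, exercise and diet need more than the 72 per group by the table's own figures. Power is about 79% and 76% with all 72 analysed, and about 75% and 71% with 65. These figures assume the Table 1 baselines, absolute 20-point increases, an uncorrected two-sided 5% test, and no dilution of the effect by carried-forward values. The shortfall is trivial for exercise before drop-out and modest for diet. The more important defect is that the primary outcome is ambiguous. This should be fixed before analysis; it does not undermine the cardiac risk comparison or the trial as a whole.

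**What to change.** Name meeting all three guidelines as the lifestyle primary outcome, alongside the cardiac risk score, in the abstract, the aims, Table 2 and the analysis section, and add it to the chi-square tests. State its power as conditional on the 9% to 29% target. Make smoking, exercise and diet secondary, and give the real power for exercise and diet from the table above. Use the Table 1 exercise definition throughout, since the 17% baseline rests on it, and align Table 2, aim (ii) and the analysis section with it.

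The cost is wording plus one further analysis of data already collected. Keeping the components as primary at 80% power would instead mean enlarging the trial to 178 participants, driven by the diet row.

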### Reason for expansion of the study

Given the proven safety record and notable benefits, it was decided to expand the study to include the post TIA population. As this population have no acquired physical disability, secondary prevention will have greater cost benefit to the health service by reducing the shared risk factors for the occurrence of stroke (currently estimated at 15% within 5 years) and development of other cardiovascular disease (CVD).

Cochrane Reviews of dietary advice, smoking cessation and stress management counselling as part of a comprehensive cardiac rehabilitation programme (CCR) in the CVD population concluded that:

• Dietary advice appears to be effective in bringing about modest beneficial changes in diet and cardiovascular risk factors over approximately 9 months but longer term effects are not known [29].

• Behavioural counselling for smoking cessation indicated that individual counselling was more effective than control. The odds ratio for successful smoking cessation was 1.56 (95% confidence interval 1.32 to 1.84). A greater effect was not detected by intensive counselling compared to brief counselling (odds ratio 0.98, 95% confidence interval 0.61 to 1.56) [30].

• Quitting smoking is associated with a substantial reduction in risk of all-cause mortality among patients with CHD. The pooled crude RR was 0.64 (95% CI 0.58 to 0.71). This 36% risk reduction appears substantial compared with other secondary preventive therapies such as cholesterol lowering which have received greater attention in recent years [31].

• Overall psychological interventions showed no evidence of effect on total or cardiac mortality, but did show small reductions in anxiety and depression in patients with CHD. Similar results were seen for stress management interventions when considered separately [32].

Although brief clinician interventions addressing physical activity and diet have been less studied than smoking cessation programmes, evidence exists that these types of interventions can influence patients to consider and adopt changes in how they eat and their physical activity levels [33,34]. Success of programmes to increase walking and other types of physical activity [34], change dietary behaviour, such as encouraging people to eat more fruit and vegetables in the 5-a-day program [36] further support clinicians' efforts to intervene in these areas.

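### Table 1, smoking row: the stated formula gives 45 per group, not 61, and the target assumes that every intervention smoker quits, so the 80% power does not carry over to smaller changes

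*Protocol article*

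**What the plan says.** The sample-size paragraph and Table 1 stand under Exclusion Criteria in the protocol article. The rows are presented as calculations with "80% power and p < 0.05 are indicated in table 1". For percentages the formula is "n > = K [P_1_(1 - P_1_) + P_2 _(1-P_2_)]/Δ^2", with K = 7.8.

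The smoking row reads "No smoking % in stroke and TIA patient population", baseline 85, target "Increase by 15" per cent, 61 per group. Recruitment is set "with an anticipated drop-out rate of 10%, 144 participants will be recruited", with "72 randomised to the intervention group and 72 to the control group". The paragraph bases this total on adherence to all three lifestyle guidelines and on the cardiac risk score.

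Three other places bear on the row:
- The abstract's Methods list habitual smoking among the primary outcome measures.
- Data Collection and Statistical Analysis states: "Categorical variables will be analysed using Chi square tests (% smoking", followed by the exercise and diet percentages.
- Reason for expansion of the study cites review evidence on individual counselling against control: "The odds ratio for successful smoking cessation was 1.56" (95% CI 1.32 to 1.84).

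**The concern.** There are two separate problems in one row.

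The first is arithmetic. A reader who applies the printed formula to the printed inputs does not get 61, although the other percentage rows check out.

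The second is the target. Starting from 85%, a rise of 15 points ends at the ceiling of 100%. The row therefore describes complete cessation in one arm and none in the other, although control participants also attend the risk-reduction lecture. Table 1 does not say this, so the row reads as if the trial had 80% power for a useful change in smoking generally. Because smoking is listed as primary and gets its own test, that impression bears on what the trial can conclude about smoking.

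**Working it through.** **Inputs.** From the sample-size paragraph and Table 1: K = 7.8, baseline non-smoking P1 = 0.85, change 15%, 72 per group, drop-out 10%. After drop-out 72 × 0.90 = 64.8, taken as 65 per arm. Expected smokers per arm: 0.15 × 72 = 10.8, about 11; 0.15 × 65 = 9.75, about 10. From Reason for expansion of the study: odds ratio 1.56. Assumed, not in the document: the control quit rate.

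**Step 1: reproduce the other percentage rows.** n = 7.8 × [P1(1 − P1) + P2(1 − P2)] / Δ², change in absolute points.

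| Row | P1 to P2 | Formula | Stated |
|---|---|---|---|
| Exercise | 17% to 37% | 72.97 | 73 |
| Diet | 21% to 41% | 79.5 | 80 |
| All three | 9% to 29% | 56.1 | 56 |

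All three agree. A relative reading of these rows gives 2,048, 1,567 and 4,291, so absolute points are plainly what the table means.

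**Step 2: the smoking row.**
- Absolute, 85% to 100%: 7.8 × (0.85 × 0.15 + 0) / 0.15² = 7.8 × 0.1275 / 0.0225 = 44.2, so 45.
- Relative, 85% to 97.75%: 7.8 × (0.1275 + 0.9775 × 0.0225) / 0.1275² = 71.7, so 72.

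Neither reading gives 61.

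**Step 3: power of the chi-square test.** Exact enumeration of two independent binomials, two-sided 5%, no continuity correction, 65 per arm, control fixed at 85% (no control smoker quits). The share of intervention smokers who must quit is (P2 − 85) / 15.

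| Intervention non-smoking | Share quitting | Power |
|---|---|---|
| 100% | all | 0.99 |
| 97.75% | 85% | 0.80 |
| 95% | two thirds | 0.49 |
| 92.5% | half | 0.27 |
| 90% | one third | 0.13 |

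So 80% power needs about 85% of intervention smokers to stop while no control smoker does.

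**Step 4: the cited odds ratio.** For a control quit rate q, the intervention quit rate q′ satisfies q′/(1 − q′) = 1.56 × q/(1 − q). Non-smoking is 0.85 + 0.15q in control and 0.85 + 0.15q′ in the intervention arm.

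| Assumed q | q′ | Non-smoking, control | Non-smoking, intervention | Difference (points) | Exact power, 65 per arm |
|---|---|---|---|---|---|
| 5% | 7.6% | 85.75% | 86.14% | 0.39 | 0.048 |
| 10% | 14.8% | 86.5% | 87.22% | 0.72 | 0.050 |
| 20% | 28.1% | 88.0% | 89.21% | 1.21 | 0.055 |
| 30% | 40.1% | 89.5% | 91.01% | 1.51 | 0.060 |

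Power is about 5–6%, close to the nominal type I error rate.

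**The case against.** The strongest reply is that the slip does no harm. The stated 61 is larger than the 45 required, 72 per group are recruited, and the total of 144 rests on the composite and the cardiac risk score. This stands: correcting the row changes neither recruitment nor power.

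A reader might infer that the wrong 61 leaves the smoking comparison with almost no power. The document does not support that. For the row's own target, exact power is about 0.99 at both 61 and 65 per arm. Low power comes from considering a smaller effect.

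A reader might also infer that the comparison cannot detect any effect the plan finds plausible. That is too strong as well. The odds ratio of 1.56 is background evidence on counselling; the protocol never adopts it as this trial's expected effect, and the programme adds supervised exercise and diet advice. Power at intermediate effects is poor but not negligible. Nor is there a firm sample size for the odds-ratio scenario: the stated formula gives about 6,000 per arm at a 30% control quit rate, about 3,600 at 50% and about 125,000 at 5%.

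Could 61 come from another method? A pooled, continuity-corrected formula gives 60, but the same correction would put the exercise row at about 84 against the stated 73. The stated formula gives 61.3 for 82% to 97%, so a different baseline may have been used; this is conjecture. Either way, the row disagrees with its printed inputs.

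Finally, primary status for smoking alone is arguable. The abstract lists it, but the second aim gives it as an example of guideline adherence, and Table 1 also contains secondary outcomes. This limits the weight of the point and favours the remedy below.

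**Conclusion.** The point holds in two parts.

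1. The figure of 61 is wrong as written. The stated formula and inputs give 45 in absolute points, or about 72 if the rise were relative. The error is conservative and the total of 144 is unaffected. This part needs no outside assumption.
2. The target is complete cessation in the intervention arm with none in control. The row's 80% power holds for that target, with room to spare, and falls steeply for less: 0.49, 0.27 and 0.13 when two thirds, half and one third of intervention smokers quit. These figures assume 65 per arm, 85% non-smoking in control and the planned chi-square test. The 5–6% under the cited odds ratio rests in addition on an assumed control quit rate of 5–30%.

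The consequence is confined to what the trial can say about smoking on its own. A non-significant result there would carry little information about a moderate effect of the counselling.

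**What to change.** - In Table 1, change 61 to 45 and state that the row assumes every intervention smoker quits and no control smoker does; or delete the row.
- Withdraw the implied 80% power for any smaller change in smoking.
- Let smoking count as primary only through the all-three-guidelines composite, which the sample-size paragraph already uses, and bring the abstract's list of primary outcomes into line.
- Report smoking alone as supportive: the proportion of baseline smokers who quit, by arm, with exact 95% confidence intervals. With about 10 or 11 smokers per arm these will be wide, and should be shown as such.

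The cost is wording, plus one withdrawn claim of 80% power. No participants or measurements are added.

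### Table 1 gives only baseline SDs for the continuous outcomes although the analysis tests change scores, and the sizes of 72 and 54 do not follow from the printed inputs

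*Protocol article*

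**What the plan says.** The bold sample size paragraph, printed under Exclusion Criteria in the protocol article, bases its calculations on detecting differences "with 80% power and p < 0.05 are indicated in table 1". For the continuous outcomes it says: "The formula for detecting a change in means was n >= 2Kσ^2^/Δ^2^K = 7.8". It does not say whether σ is the SD at one visit or the SD of change.

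The SDs in Table 1 stand under the heading "Mean (sd) of baseline measures from pilot study in stroke patients". The next column gives the pilot's mean change in the intervention group, without an SD. The three rows are:

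| Outcome | Baseline SD | Pilot mean change | Target | Stated n per group |
|---|---|---|---|---|
| Cardiac risk score (primary) | 6.80 | 1.52 | 4.0 | 72 |
| VO2 | 1.71 | 1.48 | 1.0 | 46 |
| HAD Anxiety | 3.71 | 0.86 | 1.5 | 54 |

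The recruitment figure is set "with an anticipated drop-out rate of 10%, 144 participants will be recruited", with "72 randomised to the intervention group and 72 to the control group".

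Data Collection and Statistical Analysis then states: "Change scores occurring over the 10 week trial period and between baseline and 1 year will be compared between intervention and control groups using" a list of tests. The risk score and VO2 fall under "Independent t tests and one-way ANOVA where data are interval or ratio level", provided they are normally distributed. HAD is assigned to rank tests.

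**The concern.** In the formula, σ has to be the SD of the quantity being tested. Here that is each participant's change, but the only spread shown is between people at baseline. The two can differ greatly. According to the aims in the Background, the risk score includes age, sex and diabetic status as well as blood pressure and lipids. Age and sex spread people apart at baseline but contribute almost nothing to a 10-week change, so the baseline SD is a poor stand-in for the SD of change.

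At stake is the smallest difference that the trial can detect on a primary outcome, which a reader needs in order to interpret a null result. The pilot's mean change in risk score was 1.52. If controls do not change (an assumption), whether this trial could see an effect of that size depends almost entirely on the quantity that Table 1 omits.

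**Working it through.** **Inputs.** K = 7.8, the SDs, the targets and 72 per group come from the sample size paragraph and Table 1. K = 7.8 corresponds to two-sided 5% and 80% power: (1.960 + 0.842)² ≈ 7.85. With 10% drop-out, 72 × 0.9 = 64.8, so about 65 evaluable per group. The article gives neither r nor an SD of change, so r is assumed over 0.3 to 0.9.

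**Step 1: reproduce the stated sizes** with n = 2 × 7.8 × SD²/Δ², using the baseline SDs.

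- VO2: 15.6 × 1.71²/1.0² = 45.6, so 46. Stated 46; reproduced.
- Risk score: 15.6 × 6.80²/4.0² = 45.1, so 46. Stated 72; not reproduced.
- HAD Anxiety: 15.6 × 3.71²/1.5² = 95.4, so 96. Stated 54; not reproduced.

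One-sided testing, 90% or 95% power, and inflation for 5% or 10% drop-out were also tried. None gives 72 for the risk score or 54 for HAD Anxiety. Solving backwards, 72 needs a target of about 3.17 with SD 6.80, or an SD of about 8.59 with target 4.0. The 54 fits a target of 2.0 with SD 3.71 (15.6 × 3.71²/2.0² = 53.7), or an SD of about 2.79 with target 1.5. These are only possibilities; the article does not say which, if any, was used.

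**Step 2: convert to the SD of change.** With equal SDs at both visits, SD of change = SD × √(2(1 − r)). The factor is 1 only at r = 0.5. It is below 1 for higher r and above 1 for lower r.

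**Step 3: sizes at the stated targets,** from the same formula with the SD of change:

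| Assumed r | 0.3 | 0.5 | 0.7 | 0.8 | 0.9 |
|---|---|---|---|---|---|
| Risk score, n per group for 4.0 | 64 | 46 | 28 | 19 | 10 |
| VO2, n per group for 1.0 | 64 | 46 | 28 | 19 | 10 |
| HAD Anxiety, n per group for 1.5 (t-type approximation) | 134 | 96 | 58 | 39 | 20 |

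**Step 4: what the planned groups can detect.** Detectable difference = √(15.6 × SD of change²/n). For the risk score:

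| Assumed r | 0.3 | 0.5 | 0.7 | 0.8 | 0.9 |
|---|---|---|---|---|---|
| SD of change | 8.05 | 6.80 | 5.27 | 4.30 | 3.04 |
| Detectable, 72 per group | 3.75 | 3.17 | 2.45 | 2.00 | 1.42 |
| Detectable, 65 per group | 3.94 | 3.33 | 2.58 | 2.11 | 1.49 |
| Power for 4.0, 65 per group | 81% | 92% | 99% | >99% | >99% |
| Power for 1.52, 65 per group | 19% | 25% | 38% | 52% | 81% |

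For VO2 with 65 per group, power for 1.0 is 80%, 92%, 99%, >99% and >99% over the same r.

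**The case against.** The strongest reply is that the column heading does not prove what σ was. The article leaves σ undefined, and for the primary risk score the baseline SD does not give the stated 72. A reader might infer that all three continuous sizes were built on baseline SDs. The documents support that for VO2 only; for the risk score and HAD Anxiety the basis is unknown. This part of the reply stands, but it does not rescue the table, because two of its three means rows cannot be obtained from their own printed inputs.

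A reader might also infer that the trial is underpowered. The figures do not support that for the risk score or VO2: at the lowest assumed r of 0.3, both need 64 per group, and about 65 remain after drop-out. Planning on a baseline SD when r is unknown is common and is conservative whenever r exceeds 0.5. The make-up of the risk score points towards a high r at 10 weeks. This part also stands, and it limits the consequence to a misstated detectable difference.

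Finally, it is tempting to say that the pilot's SD of change is already in hand. Table 1 shows that before-and-after changes were calculated, so it should be obtainable, but the article does not report it.

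**Conclusion.** The point holds in a limited form. The variability shown in Table 1 is not that of the planned comparison. The VO2 row demonstrably rests on a baseline SD, and the risk score (72 against 46) and HAD Anxiety (54 against 96) rows do not follow from their printed inputs.

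The likely consequence is a detectable difference that is misstated, and probably too large, rather than a shortage of participants. For the risk score, the true figure with about 65 evaluable per group lies between 3.94 and 1.49, against the printed 4.0. The claim of at least 80% power covers the risk score and VO2 only. For HAD Anxiety, a secondary outcome, the t-type formula asks for more than 65 per group at r = 0.5 or below, and it is only approximate for the planned rank test.

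All of this assumes equal SDs at both visits, 10% loss and r between 0.3 and 0.9. The value of r may also differ between the 10-week and 1-year comparisons.

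**What to change.** - Define σ in the sample size paragraph as the SD of change. Take it from the pilot's before-and-after data if available; otherwise state an assumed r and show the range. If the analysis is to adjust for baseline, use the residual SD given baseline instead.
- Recompute the three means rows with that SD. Reconcile the 72 and the 54 with the formula by correcting the SD, the target or the size, whichever was misprinted or miscalculated. Note beside the HAD row that a rank test is planned and the formula is approximate.
- Restate the difference detectable at 80% power with 72 randomised, about 65 evaluable, per group for the risk score and VO2.

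The cost is a recalculation and a corrected table. Recruitment does not change.
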